### Randomization

All patients will be randomized into either a routine treatment group or a high-dose atorvastatin group. These patients will be subjected to a stratified blocked randomization method that will assign individuals to treatment groups based upon age(> 70 years or not) and presentation (symptomatic or asymptomatic). Random number generation by a dedicated software program will then be used to assign patients to groups with 1:1 matching grouping and no cross-grouping are permitted.

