### Sample Size Estimates

The open-source Open-EPI v3.03 software was used for sample size calculations for the present study. The test level α is 0.05 (two-sided test), and the test efficiency Power (1-β) is 0.08. Based upon findings in the abovementioned meta-analysis and the ARMYDA-9 CAROTID study, we estimated a primary endpoint incidence of 40% in routine-dose control group patients. In contrast, the incidence in the high-dose treatment group, who will undergo therapy longer than did patients in the ARMYDA-9 CAROTID study, was estimated to be lower at 15%. Given a 1:1 control to test group ratio, it was estimated that the control group would require 56 test cases. Given a predicted 15% dropout rates, a required sample size of 65 was calculated for both groups, yielding an overall sample size of 130.

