### Statistical Analyses

All categorical variables will be given as percentages, while continuous variables will be means ± standard deviations. Chi-squared tests or Fisher's exact tests will be used to compare categorical variables, whereas continuous variables will be analyzed via *t*-tests or a *U*-tests.

These statistical methods will be used to compare whether there are any differences between the control and test groups at baseline, and whether there are any differences in perioperative ischemic brain injury incidence between these groups. *P* < 0.05 will be the significance threshold. In addition, univariate and multivariate logistic regression analyses will be used as a means of identifying any risk factors associated with the incidence of perioperative ischemic brain injury (primary endpoint and partial secondary endpoint) in CAS patients. Prespecified subgroup analysis will be conducted according to whether age is > 70 years and whether symptomatic or not.

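### The primary comparison does not use the randomisation strata: a stratified test would be a nearly free, small improvement if age and symptom status are prognostic

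*Protocol article*

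**What the plan says.** Under Randomization, the article says that patients will be "subjected to a stratified blocked randomization method that will assign individuals to treatment groups based upon age" (above 70 or not) and presentation (symptomatic or asymptomatic). That makes four strata, with 1:1 allocation.

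Under Statistical Analyses, "Chi-squared tests or Fisher's exact tests will be used to compare categorical variables". The same methods are then assigned to baseline comparisons and to "whether there are any differences in perioperative ischemic brain injury incidence between these groups". No stratified or adjusted test is named for that comparison. Nothing says when Fisher replaces chi-squared, or whether chi-squared carries a continuity correction.

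Univariate and multivariate logistic regression is also planned on the primary endpoint. Its stated purpose is to identify risk factors, and no covariate list is given. The stratification factors return only as subgroups: "Prespecified subgroup analysis will be conducted according to whether age is" above 70, and by symptom status.

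**The concern.** Stratified allocation makes the arms more alike on the stratification factors than simple randomisation would. If those factors predict the outcome, the true variance of the difference between arms is smaller than the variance a crude 2x2 test assumes. The crude test then rejects a true null hypothesis less often than 5% and can miss some real effects that a stratified test would detect.

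At the planned rates only about 31 primary events are expected (0.40 x 56 + 0.15 x 56 = 22.4 + 8.4 = 30.8), so a borderline result is possible. Because the article does state its primary comparison, this is an analysis choice that can be judged as written, not merely a detail left for later.

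**Working it through.** **Inputs from the article (Sample Size Estimates, Randomization).** Two-sided alpha 0.05; "we estimated a primary endpoint incidence of 40% in routine-dose control group patients"; the high-dose rate "was estimated to be lower at 15" per cent; 1:1 allocation; 56 per arm before dropout; 15% dropout; 65 per arm; four strata. The printed power ("the test efficiency Power (1-β) is 0.08") is taken as a slip for 0.80, because 0.08 would need only 3 per arm, or 9 with continuity correction.

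**Inputs assumed.** Each factor is present in half of the patients. Both factors have the same odds ratio for the outcome, varied from 1 to 3. The documents give neither prevalence nor prognostic strength.

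**Step 1: reproduce the plan's sample size.** With mean rate (0.40 + 0.15)/2 = 0.275:

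n = [1.960 x sqrt(2 x 0.275 x 0.725) + 0.8416 x sqrt(0.40 x 0.60 + 0.15 x 0.85)]^2 / 0.25^2 = (1.2377 + 0.5102)^2 / 0.0625 = 48.9, so 49 per arm.

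With continuity correction: (48.88/4) x [1 + sqrt(1 + 4/(48.88 x 0.25))]^2 = 12.22 x 2.152^2 = 56.6, so 57 per arm against the stated 56. For dropout, 56 x 1.15 = 64.4, so 65 as stated (56/0.85 = 65.9 would give 66). The plan's figures reproduce within rounding.

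**Step 2: why the crude test is conservative.** The crude test uses variance p(1 - p). With strata balanced across arms, the true variance is the mean over strata of p_k(1 - p_k), which equals p(1 - p) minus the between-stratum variance of p_k. Take OR 3 per factor and an overall rate of 40%. The stratum rates are about 17.3%, 38.6%, 38.6% and 65.4%, and their variance is about 0.029. The ratio of true to assumed variance is 1 - 0.029/0.24 = 0.88. The nominal cut-off of 1.96 then acts as 1.96/sqrt(0.88) = 2.09, which is a two-sided level of about 3.7%. A simulation with exact balance (200,000 runs, 56 per arm) gives 3.4%.

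**Step 3: exact balance, no dropout.** In that simulation, power at 40% vs 15% for CMH against crude chi-squared is 0.858 vs 0.859 (OR 1), 0.865 vs 0.862 (OR 1.5), 0.872 vs 0.864 (OR 2) and 0.892 vs 0.872 (OR 3).

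**Step 4: allow for dropout.** Losses disturb the balance within strata and so weaken the effect. Two separate simulations were run. Run A has 130 randomised in assumed blocks of 4 with 14% random loss. Run B has about 15% loss. Difference is CMH minus crude, in percentage points.

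| OR per factor | Run A power, crude / CMH | Run B power, crude / CMH | Difference, A / B | Crude type I error at 40%, A / B |
|---|---|---|---|---|
| 1 | 0.858 / 0.854 | 0.861 / 0.856 | -0.4 / -0.5 | 0.051 / 0.051 |
| 1.5 | 0.862 / 0.862 | 0.863 / 0.862 | 0.0 / -0.1 | 0.049 / 0.050 |
| 2 | 0.863 / 0.869 | 0.865 / 0.872 | +0.6 / +0.7 | 0.045 / 0.045 |
| 3 | 0.869 / 0.888 | 0.866 / 0.886 | +1.9 / +2.0 | 0.040 / 0.039 |

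The CMH type I error in Run A stays between 0.049 and 0.051. With assumed prevalences of 40% and 70% instead of equal ones, OR 2 gives 0.862 (crude) vs 0.867 (CMH).

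**Step 5: the open choice of test.** By exact enumeration at 56 per arm, power is 0.859 for uncorrected chi-squared and 0.808 for Fisher. At a common 27.5% rate, type I error is 0.050 and 0.031. As an illustration, 22/55 vs 12/55 gives p = 0.039 by uncorrected chi-squared and p = 0.063 by Fisher. The smallest expected count in that table is (22 + 12)/2 = 17.

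**The case against.** The strongest reply is that nothing here is invalid. Any error is towards caution, and both named tests meet the planned 80% power at 56 per arm. With no prognostic effect the stratified test is marginally worse, and up to about OR 1.5 there is nothing to gain. All of this stands, and it limits the point to a small gain in efficiency.

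Four stronger readings are tempting, and the documents do not support them.

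- A reader might infer that the crude test definitely loses power. That depends on a prognostic strength the article does not give.
- A reader might infer that the open choice between chi-squared and Fisher puts the trial's verdict at risk. The sentence is generic. It also covers baseline variables and rare outcomes such as death, where Fisher is natural. On the customary small-expected-count reading, chi-squared applies at the planned rates and in the 22/55 vs 12/55 example. The missing rule is mostly detail.
- A reader might infer that subgroups will be judged by separate p-values. The article says only that subgroup analyses will be done, so no fault is stated.
- A reader might infer that stratification brings the trial nothing. It still secures baseline balance and supports the subgroup analyses on the same factors.

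One might also say that the multivariate logistic regression already adjusts for the strata. It may, but its covariates are not listed and its stated purpose is not the treatment comparison.

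**Conclusion.** The point holds as a low-cost improvement, not as a flaw that threatens the result. The primary comparison as written ignores the factors used to randomise. Over assumed odds ratios of 1 to 3 per factor, and with about 15% dropout, the crude test's type I error runs from about 5.1% down to 3.9%. Using the strata changes power by between roughly -0.4 and +2 percentage points. These figures rest on the article's 40% and 15% rates, random loss, the same odds ratio for both factors, and each factor present in half of the patients. No inflated false-positive rate and no shortfall against the planned power follow from this point.

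**What to change.** In Statistical Analyses, name one primary test that uses the randomisation strata. Either of these would serve:

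- a Cochran-Mantel-Haenszel test stratified by age above 70 and symptomatic status, with a stratified risk difference and 95% CI; or
- a logistic regression with treatment and both factors as terms.

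Keep the unstratified test as a sensitivity analysis. Naming a single primary test also settles the choice between chi-squared and Fisher.

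The cost is one paragraph of wording. Both factors must be known at randomisation, so no new data are needed. The statistical cost is a power loss of about half a percentage point at most if the factors turn out not to be prognostic.

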### Patient and Public Involvement

There was no patient or public involvement in the design of this clinical trial protocol.

## Discussion

At present, it remains unclear as to whether patients of Chinese ethnicity undergoing CAS receive the same benefits from high-dose atorvastatin treatment as do patients from Western countries. To date, no published randomized controlled trials (RCTs) addressing this issue have been reported, and as such, the present study is of evident clinical importance.

Atorvastatin is currently the most commonly used drug administered to patients suffering from cardiovascular and cerebrovascular diseases. Its administration is associated with significant reductions in blood lipid levels and with an associated decrease in the risk of myocardial infarction, stroke, and death. Currently, patients with cardiovascular and cerebrovascular diseases, including patients undergoing CAS, are treated with a low (10–20 mg/day) dose of atorvastatin. However, some studies have identified a number of potentially neuroprotective benefits to the administration of a higher 80 mg/day atorvastatin dosing regimen, which is associated with the protection of the vascular endothelium, blood vessel dilation, and reduced risk of thrombosis. In individuals with ischemic cerebrovascular disease, the stroke prevention by aggressive reduction in cholesterol levels (SPARCL) trial, which assessed the ability of intensive atorvastatin treatment to prevent stroke recurrence, confirmed that an 80 mg/day atorvastatin dose was able to effectively prevent the recurrence of stroke and adverse cardiac events in patients that have suffered from TIA or stroke (9). To date, the atorvastatin remains the only statin that has been shown to effectively prevent stroke in RCT studies.

To date, relatively few studies have thoroughly examined statin use in patients undergoing CAS. Recent non-randomized studies have found that the use of statins may be associated with reduced rates of adverse events including TIA, stroke, myocardial infarction, new ischemic foci formation, and death following CAS when comparing patients using statins to those not using statins. Similarly, randomized studies have found statin used to be associated with lower rates of stroke, TIA, new ischemic foci formation, myocardial infarction, and death following CAS (10, 11).

Studies of Western populations have observed a 17% incidence of new ischemic lesions in patients treated with 120 mg atorvastatin prior to CAS, as detected via DW-MRI (7). Additional research suggests that micro-emboli detachment can still occur 1 day post-CAS. As such, the use of atorvastatin for a longer duration both pre- and post-CAS may be associated with lower rates of new ischemic lesion formation. As previous studies have demonstrated that 3 days of continuous oral dosing with atorvastatin is sufficient to achieve steady-state plasma concentrations in patients with significant reductions in LDL levels in treated patients (12, 13), we plan to provide patients in this study with a loading dose regimen wherein they begin taking an oral loading dose of atorvastatin 3 days prior to CAS and continue to do so for 3 days postoperatively. The goal of this approach is to take into account both the safety of patients and the practicality of implementing such a dosing regimen.

## Ethics Statement

The studies involving human participants were reviewed and approved by Beijing Hospital Ethics Committee. The patients/participants provided their written informed consent to participate in this study.

## Appendix

**Table T1:** **Trial registration data set**.

**Data category**	**Information**
Primary registry and trial identifying number	ClinicalTrials.gov NCT03079115
Date of registration in primary registry	March 14, 2017
Secondary identifying numbers	121-2016006
Source (s) of monetary or material support	Beijing Hospital
Primary sponsor	Beijing Hospital
Secondary sponsor (s)	
Contact for public queries	[name] [contact]
Contact for scientific queries	[name]. [contact]
Public title	Efficacy of Two Different Doses of Atorvastatin for Prevention of Periprocedural Ischemic Brain Damage in Chinese Patients Undergoing Carotid Artery Stenting (CAS)
Scientific title	Effects of High dose of atorvastatin for Preventing periprocedural Ischemic brain damage in patients undergoing Carotid Artery Stenting (PICAS) in China: A Randomized Controlled Clinical Trial
Countries of recruitment	CHINA
Health condition (s) or problem(s) studied	Carotid Stenosis, Carotid artery stenting, High-dose statin therapy
Intervention (s)	High-dose Atorvastatin Arm: (80 mg/day from 3 days before to 3 days after CAS, and thereafter 20mg/day until 30 days after CAS) Conventional-dose Atorvastatin Arm: (20 mg/day from 3 days before to 30 days after CAS).
Key inclusion and exclusion criteria	Ages Eligible for Study: 40 Years to 90 Years (Adult, Older Adult) Sexes Eligible for the study: both Inclusion criteria: ≥ 50% stenosis of the internal carotid artery in symptomatic patients; or ≥ 70% stenosis of the internal carotid artery in asymptomatic patients received statin therapy for ≥ 2weeks before inclusion Exclusion criteria: nonatherosclerotic carotid disease (dissection, radiation-induced stenosis) received endovascular procedure within 30 days before inclusion CAS during the procedure of urgent endovascular therapy for acute ischemic stroke
Study type	Interventional (Clinical Trial) Allocation: randomized Intervention model: parallel assignment Masking: single(outcomes assessor) Primary purpose: treatment
Date of the first enrolment	August 21, 2017
Target sample size	130 participants
Recruitment status	Recruiting
Primary outcome (s)	Cumulative incidence of new ischemic lesion on post-CAS cerebral DW-MRI, TIA or ischemic stroke within 30 days after CAS
Key secondary outcomes	incidence of new ischemic lesion on post-CAS DW-MRI; number of new lesions on post-CAS DW-MRI; incidence of new lesion > 5 mm on post-CAS DW-MRI
